## Materials and methods

The FORECAST study is an ongoing ambispective case-control study conducted at the National Institute of Neurosciences and Hospital (NINS&H), Bangladesh, in collaboration with the Institute of Cardiovascular Research, Royal Holloway, University of London, UK. This design allows for comprehensive characterization of stroke risk factors while maintaining feasibility within the Bangladeshi healthcare infrastructure between May 2022 and April 2026. The primary objective is to develop an AI-based risk prediction model that identifies independent predictors of stroke occurrence and poor long-term outcomes among Bangladeshi individuals. The study will also utilize explainable AI techniques to enhance the clinical interpretability of CT and MRI brain imaging findings, leveraging recent advances in stroke prediction modeling, with an anticipated accuracy rate exceeding 90%.

The study has received ethics approval from the institutional review boards of the National Institute of Neurosciences and Hospital (NINS&H), Dhaka, Bangladesh (reference number IRB/NINS/2025/492). Given the retrospective nature of case identification, a waiver of informed consent has been granted for historical data analysis, while prospective participants will provide written informed consent. Data anonymization follows international standards with secure storage and restricted access protocols. Written informed consent will also be obtained from a legal representative if the patient is unconscious or intubated.

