Inclusion criteria encompass complete medical records availability and Bangladeshi residency for ≥5 years, while exclusion criteria include incomplete clinical data and previous stroke history for first-ever stroke analyses. Cases include adult patients (≥18 years) with acute ischemic or hemorrhagic stroke confirmed by a neuroimaging scan, either a CT/MRI scan, evaluated by two experts (neurologist and intervention radiologist). Stroke diagnosis will follow American Stroke Association (ASA) guidelines, confirmed by clinical evaluation and CT or MRI imaging. All patients with any form or severity of stroke, including mild, severe, prior, recurrent, critically ill, or intubated cases, will be included to reduce selection and reporting bias. Individuals with major comorbidities, such as other neurological disorders (e.g., brain tumors), severe systemic illnesses (e.g., cancer), secondary strokes due to other conditions (e.g., endocarditis, trauma), or those taking medications affecting stroke risk, will be excluded. Controls comprise age and sex-matched healthy adults without stroke history, recruited from hospital visitors and community health facilities, ensuring representative sampling across urban and rural populations. Controls will be 18 years or older, have no history of stroke, and must provide written informed consent. Hospitalized individuals are not eligible as controls. If spouse controls are unavailable, age- and sex-matched community volunteers will be recruited, with gender balance ensured through equal representation or sex stratification in analysis. The study will maintain equal proportions of males and females in both groups to address sex-related differences in stroke risk. Controls will be selected from the same geographic and socioeconomic backgrounds as cases to minimize population stratification and ensure comparability in environmental factors, lifestyle, and medication use.

The study will enroll 4,000 participants, comprising 2,000 stroke cases and 2,000 matched controls. Sample size calculations utilized established formulas for case-control studies with binary exposure, assuming 80% power, 5% significance level, and expected stroke prevalence of 35% in the exposed group versus 15% in the unexposed group [12,13]. This sample size ensures adequate power to detect clinically meaningful associations while accounting for potential data missingness and subgroup analyses. The formula for case-control studies with binary exposure:

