n = [P₁(1-P₁) + P₀(1-P₀)] × (Zβ + Zα/2)² / (P₁ - P₀)²

where power (1-β): 80% (Zβ = 0.84); α: 5% (Zα/2 = 1.96), expected stroke prevalence in exposed group (P₁): 35%, expected stroke prevalence in unexposed group (P₀): 15%, and minimum detectable odds ratio: 2.0.

Calculation:

n = [0.35×0.65 + 0.15×0.85] × (0.84 + 1.96)² / (0.35 - 0.15)²

n = [0.2275 + 0.1275] × 7.84 / 0.04

n = 0.355 × 196 = 69.58 ≈ 1,740 per group

Accounting for 15% loss to follow-up and missing data: 1,740 × 1.15 = 2,000 per group

The total sample size will comprise 4,000 participants, divided into 2,000 cases and 2,000 controls.

Comprehensive data collection encompasses sociodemographic variables (age, sex, education level, rural-urban residence, occupation, income), clinical parameters (blood pressure, glucose levels, lipid profiles, body mass index), comorbidities (hypertension, diabetes mellitus, atrial fibrillation, coronary artery disease), lifestyle factors (smoking, alcohol consumption, physical activity), and mental health assessments using validated instruments including the Generalized Anxiety Disorder-7 (GAD-7) and Patient Health Questionnaire-9 (PHQ-9) scales [14,15]. Outcome measures include stroke occurrence (primary outcome) and long-term functional outcomes assessed using the Modified Rankin Scale at 90 days post-stroke (secondary outcome) [16]. Additional outcomes encompass stroke recurrence, mortality, and healthcare utilization patterns to provide comprehensive prognostic information.

The study will implement an ensemble machine learning approach integrating multiple algorithms to optimize prediction accuracy [17]. The modeling framework comprises four specialized modules: a sociodemographic module utilizing neural networks for processing education, rural-urban status, and socioeconomic factors; a clinical risk module employing random forest algorithms for traditional risk factors; a mental health module using gradient boosting to capture anxiety-depression patterns; and an outcome prediction module combining all inputs for final risk stratification [18,19].

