The clinical implications of accurate AI-based risk prediction extend beyond individual patient care to encompass population health strategies and healthcare resource allocation. By identifying high-risk individuals before stroke event occurrence, clinicians can implement targeted interventions, including intensive blood pressure management, anticoagulation therapy, lifestyle modifications, and mental health support, potentially preventing thousands of strokes annually [12,30]. Moreover, the explainable AI components of the FORECAST model will enhance clinical adoption by providing transparent, interpretable risk assessments that support shared decision-making between patients and healthcare providers, ultimately improving treatment adherence and outcomes. While the proposed study is promising, there are several limitations to consider. The sample size may not fully reflect the clinical and environmental diversity of the Bangladeshi population, which could affect how well the AI-based stroke risk prediction model applies to broader groups. The AI-based risk prediction model offers a powerful tool for identifying potential risk factors and predicting long-term poor prognosis among stroke patients in Bangladesh. Its strength lies in the ability to analyse large, complex datasets, uncovering subtle patterns that may not be apparent through traditional statistical methods. By integrating demographic, clinical, and imaging data, the model can provide personalised risk assessments to support early intervention and improve patient outcomes. However, limitations include dependence on data quality and completeness, as inconsistencies or biases in local healthcare records may reduce accuracy. In addition, the model’s generalisability may be constrained by limited external validation, making it essential to test and refine it across diverse populations and clinical settings within Bangladesh. Data will mostly come from selected hospitals, so rural or underserved populations may not be represented, especially where healthcare access and reporting differ. Further, the AI model’s accuracy depends on data quality, which could be affected by inconsistent diagnostic criteria, missing data, differences in imaging protocols, or variations in lab measurements. Moreover, without external validation using independent, multi-center groups, the model’s usefulness outside the study population is limited. The AI algorithm’s complex nature may also make it harder to interpret results for clinical decisions.

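### The stroke-occurrence model is not confined to pre-onset predictors, so GAD-7/PHQ-9 scores and clinical values taken at study entry can act as predictors although in cases they follow the stroke

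*Protocol article*

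**What the plan says.** All references are to the protocol article.

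- **Design and entry (Materials and methods).** "The FORECAST study is an ongoing ambispective case-control study conducted at the National Institute of Neurosciences and Hospital (NINS&H), Bangladesh". A case is an adult "with acute ischemic or hemorrhagic stroke confirmed by a neuroimaging scan, either a CT/MRI scan, evaluated by two experts". All severities are taken, "including mild, severe, prior, recurrent, critically ill, or intubated cases, will be included to reduce selection and reporting bias". Controls are healthy, stroke-free people who are not in hospital.
- **Predictors (Materials and methods).** Besides sociodemographic, comorbidity and lifestyle items, the study records blood pressure, glucose, lipids and body mass index, and "mental health assessments using validated instruments including the Generalized Anxiety Disorder-7 (GAD-7) and Patient Health Questionnaire-9 (PHQ-9) scales". No time of measurement relative to onset is given for any of them.
- **Model (Materials and methods).** Anxiety and depression have their own gradient-boosting module, and traditional risk factors have a random-forest module. A final module takes in everything. Stroke occurrence is the primary outcome and the 90-day modified Rankin Scale the secondary one. The article does not assign different predictors to the two.
- **Claimed use.** The Discussion describes preventive action: "By identifying high-risk individuals before stroke event occurrence". The Results section expects new knowledge on how mental health relates to stroke. The Discussion justifies the mental-health variables by evidence that depression and anxiety raise stroke risk.
- **Limitations (Discussion).** These cover data quality, generalisability and interpretability. Reverse causation is not among them.

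**The concern.** A model of stroke occurrence is useful only if its inputs describe people before they have a stroke. Here a person becomes a case by having had one. A PHQ-9 given on the ward, or a blood pressure or glucose taken at admission, is in part an effect of the stroke. The same measurement in a healthy control reflects no such event. A flexible learner will use that difference whether or not it existed before onset.

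Two claims are at stake. One is the accuracy of the primary model, which is expected to exceed 90%. The other is the claim that mental health contributes to stroke risk, because post-event scores cannot separate cause from consequence. The planned checks do not help. Ten-fold cross-validation splits the same data, so every fold carries the artefact. SHAP and LIME would rank the affected variables as important features.

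**Working it through.** **Step 1: timing.** The article states no measurement times, so the order of events has to be derived.

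| Element | Cases | Controls |
|---|---|---|
| Condition for entry | Acute stroke already confirmed by CT or MRI | No stroke history, not hospitalised |
| GAD-7/PHQ-9 given by the study | After the event | No event |
| Blood pressure, glucose, lipids at entry | After the event | No event |
| Values from earlier records | May precede the event; nothing requires their use | Not described |
| Self-report scales when unconscious or intubated | Missing or by proxy | Does not arise |

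The last row follows from enrolling such patients, with consent from a legal representative. Whether a score is absent or given by proxy is thus itself related to case status. Multiple imputation (Statistical analysis) does not repair this: within cases, a missing score would be filled from other cases' scores, which are themselves post-stroke if taken at entry.

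**Step 2: possible size for a screening score.** The plan gives no figure to reproduce for this point. Its benchmarks, from the sample-size paragraph, are a minimum detectable odds ratio of 2.0 and proportions of 35% and 15%, which imply

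OR = (0.35/0.65) / (0.15/0.85) = 3.05.

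Suppose that pre-stroke mood has no effect on stroke, so that any excess of positive screens in cases arises after onset. With p1 the proportion positive in cases and p0 in controls,

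spurious OR = [p1/(1 − p1)] / [p0/(1 − p0)].

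All prevalences below are assumptions; the article gives none.

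| Positive in cases | Controls 10% | Controls 15% |
|---|---|---|
| 20% | 0.2500/0.1111 = 2.25 | 0.2500/0.1765 = 1.42 |
| 30% | 0.4286/0.1111 = 3.86 | 0.4286/0.1765 = 2.43 |
| 40% | 0.6667/0.1111 = 6.00 | 0.6667/0.1765 = 3.78 |

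Five of the six values reach 2.0. Three reach 3.05 (3.86, 6.00 and 3.78). The value 1.42 reaches neither.

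**Step 3: possible size for model performance.** Take four predictors (GAD-7, PHQ-9, blood pressure, glucose) with no pre-stroke association, each shifted by d standard deviations after stroke. Assume normal distributions with equal variance, independence, and equal group sizes. The combined shift is D = d√4 = 2d, with AUC = Φ(D/√2) and best-cut accuracy = Φ(D/2).

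| d (assumed) | D | AUC | Accuracy |
|---|---|---|---|
| 0.2 | 0.4 | 0.61 | 58% |
| 0.5 | 1.0 | 0.76 | 69% |
| 0.8 | 1.6 | 0.87 | 79% |
| 1.0 | 2.0 | 0.92 | 84% |

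An accuracy of 90% needs D = 2.56, so none of these shifts reaches the target alone. If GAD-7 and PHQ-9 move together, independence overstates the combined shift.

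**The case against.** The strongest reply is that post-stroke timing is inferred. The sentence naming the instruments gives no time, a journal article condenses a fuller document, and the study has a retrospective part: "Given the retrospective nature of case identification, a waiver of informed consent has been granted for historical data analysis". Complete medical records are required, so some pre-stroke values may exist. This stands as a limit on the wording. A reader might infer that every predictor in cases is recorded after stroke, and the article does not say so. But the point does not rest on a missing visit schedule. Case definition, primary outcome, instruments and the pooled framework are all stated. An analysis plan could restrict the predictors, but it cannot turn a questionnaire given after stroke into a pre-stroke measurement.

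A reader might also infer that scans drive the occurrence model and that controls are not scanned. The Discussion does say "By integrating demographic, clinical, and imaging data, the model can provide personalised risk assessments", but imaging is not in the data-collection list or named in any of the four modules. The surrounding text also concerns prognosis after stroke, where imaging is a proper input. Control imaging is not described, which is not the same as ruled out. Nor does the article say how controls' data are collected, beyond written consent.

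A third tempting reading is that the spurious effect always exceeds the plan's design effects. The tables above do not bear that out.

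The plan does exclude incomplete clinical data. Applied to the scales, that rule would remove the severe cases that the eligibility text sets out to keep, so it does not resolve the missing scores.

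Finally, sociodemographic items, known comorbidities and lifestyle history are much less exposed, and post-stroke values are legitimate for the 90-day outcome. Both limits are accepted.

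**Conclusion.** The concern holds for the primary stroke-occurrence model. As written, the plan lets post-onset measurements in cases predict the event that preceded them, then presents the result as pre-stroke risk and as evidence on mental health, without naming reverse causation. The conclusion rests on one inference: that study-administered scales and entry clinical values are taken at or after enrolment unless drawn from earlier records.

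The size is illustrative only. Under the assumed prevalences the spurious odds ratio runs from 1.42 to 6.00, and several values, not all, reach the plan's 2.0 or the implied 3.05. Under the assumed shifts, timing alone could supply a substantial part of the apparent accuracy, but not all of the 90% target. The secondary 90-day model is not affected. Because the primary model and its main claim are, this should be settled before that model is fitted.

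**What to change.** 1. Define separate predictor sets for the two outcomes.
2. Restrict the primary occurrence model to collected variables that refer to a time before onset and can be obtained alike in both groups: sociodemographic items, comorbidity history and lifestyle history. Admit clinical values only where pre-onset readings are already recorded comparably in cases and controls.
3. Keep entry GAD-7/PHQ-9, acute-phase clinical values and any imaging for the case-only 90-day modified Rankin Scale model.
4. As a sensitivity analysis, report occurrence performance with and without the mental-health module and the acute values.
5. Do not interpret post-onset scores, including their SHAP or LIME rankings, as pre-stroke risk factors, and name reverse causation as a limitation.

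This uses data already being collected. Newly gathering pre-stroke readings or diagnosed anxiety and depression is not proposed. Those items are not in the variable list, and the Introduction itself describes stigma and scarce mental-health resources, so their ascertainment could differ between cases and controls.

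The cost is a lower apparent accuracy for the occurrence model, a weaker mental-health claim and some extra model runs.

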Feature selection will employ correlation-based, mutual information-based, and wrapper-based methods to identify optimal predictor combinations while minimizing overfitting [20]. The study will address data imbalance issues through the Synthetic Minority Oversampling Technique (SMOTE) and other resampling methods to ensure robust model performance across all risk categories [21]. Model validation will utilize k-fold cross-validation (k = 10) with stratified sampling to ensure representative distribution across subgroups [22]. Performance evaluation will encompass accuracy, sensitivity, specificity, area under the receiver operating characteristic curve (AUC-ROC), and F1-score metrics, with target performance exceeding 90% accuracy based on recent advances in stroke prediction modeling [23,24].

To enhance clinical interpretability and trust, the study will integrate explainable AI techniques, including Shapley Additive Explanations (SHAP) and Local Interpretable Model-Agnostic Explanations (LIME) [25]. These methods will provide insights into feature importance, individual prediction explanations, and model decision-making processes, facilitating clinical adoption and regulatory approval (Figure 1).

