**Figure 1 FIG1:**
[figure not shown]
Dummy flowchart showing case-control recruitment to dissemination GAD: generalized anxiety disorder; PHQ: Patient Health Questionnaire; AI: artificial intelligence; AUROC: area under the receiver operating characteristic curve; mRS: Modified Rankin Scale Image created by the authors

Statistical analysis

Statistical analyses will employ appropriate methods for case-control studies, including conditional logistic regression for matched data and multiple imputation for missing values. Subgroup analyses will examine risk patterns across rural-urban populations, educational strata, and age groups to identify population-specific risk factors. Model calibration will be assessed using Hosmer-Lemeshow goodness-of-fit tests and calibration plots [26].

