## Results

Expected results and clinical impact

The FORECAST study will deliver the first AI-based stroke prediction model (Figure 2) specifically designed for Bangladeshi populations, with expected clinical and scientific impacts encompassing improved risk stratification leading to targeted prevention strategies, novel insights into mental health-stroke associations in South Asian populations, and cost-effective screening tools for resource-limited settings [27]. The model will provide personalized risk scores with confidence intervals, enabling clinicians to make evidence-based decisions regarding preventive interventions and resource allocation.

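### SMOTE has nothing to do in the 1:1 primary data set, and wherever it did act it would distort the predicted risks the plan means to check and report

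*Protocol article*

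**What the plan says.** All references are to the protocol article.

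- **Design (Materials and methods).** "The study will enroll 4,000 participants, comprising 2,000 stroke cases and 2,000 matched controls".
- **Outcomes (Materials and methods).** "Outcome measures include stroke occurrence (primary outcome) and long-term functional outcomes assessed using the Modified Rankin Scale at 90 days post-stroke (secondary outcome"). The text continues: "Additional outcomes encompass stroke recurrence, mortality, and healthcare utilization patterns". No Rankin cut-off and no expected rate is given for any of these outcomes.
- **Resampling (Materials and methods, model development).** "The study will address data imbalance issues through the Synthetic Minority Oversampling Technique (SMOTE) and other resampling methods". The stated aim is robust performance in all risk categories. The sentence gives no outcome, target ratio, SMOTE variant or later correction. The next sentence plans stratified ten-fold cross-validation.
- **Calibration (Statistical analysis).** "Model calibration will be assessed using Hosmer-Lemeshow goodness-of-fit tests and calibration plots".
- **Use of the predictions (Results, expected results and clinical impact).** "The model will provide personalized risk scores with confidence intervals", which clinicians are to use when deciding on prevention and resources.

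**The concern.** Resampling is planned for a problem that the design has already removed from the full primary data set. For the other outcomes, where one class may be much smaller, oversampling changes the event rate that the model learns from. Its probabilities then describe the artificial mix and not the patients. A ranking measure such as AUC hardly registers this, but a calibration plot or a risk score given to a clinician does. The same plan therefore commits to a step that disturbs predicted probabilities, to an assessment of those probabilities and to their clinical use, and it does not say how the three fit together. At stake is whether an individual risk figure from the model can be read as a risk.

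**Working it through.** **1. Primary outcome.** The inputs are 2,000 cases and 2,000 controls, from Materials and methods. The case share is 2,000 / 4,000 = 50%. Synthetic records needed to reach 1:1 are 2,000 − 2,000 = 0. (The article's derivation of the group size is a separate matter; only the ratio is used here.)

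**2. Expected shift where SMOTE acts.** Let q be the true event rate, below 50%. Oversampling the minority class to 1:1 changes the odds in the training data from q/(1 − q) to 1, so predicted odds are multiplied by about (1 − q)/q:

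- q = 10%: 0.90/0.10 = 9.0
- q = 20%: 0.80/0.20 = 4.0
- q = 30%: 0.70/0.30 = 2.3
- q = 40%: 0.60/0.40 = 1.5
- q = 50%: 0.50/0.50 = 1.0, no shift

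For one patient: at q = 20%, a true risk of 10% has odds 0.10/0.90 = 0.111. Multiplied by 4.0 this is 0.444, which corresponds to a predicted risk of 0.444/1.444 = 31%.

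**3. Simulation.** The assumptions, none of them from the article, are: 2,000 training patients and 2,000 untouched test patients, five normally distributed predictors, a logistic model, SMOTE with five neighbours to 1:1 in the training data only, and 50 replicates. Results in the test patients:

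| Assumed event rate | Observed | Mean predicted, no SMOTE | Mean predicted, SMOTE | AUC, no SMOTE / SMOTE | Hosmer-Lemeshow p < 0.05, no SMOTE / SMOTE |
|---|---|---|---|---|---|
| 10% | 10.0% | 10.1% | 42.2% | 0.735 / 0.734 | 10% / 100% |
| 20% | 20.0% | 20.2% | 44.8% | 0.731 / 0.731 | 12% / 100% |
| 30% | 30.1% | 30.0% | 46.5% | 0.731 / 0.731 | 16% / 100% |
| 40% | 40.5% | 40.0% | 48.3% | 0.729 / 0.729 | 10% / 100% |
| 50% | 50.1% | 50.3% | 50.6% | 0.726 / 0.726 | 12% / 10% |

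Trained on the data as sampled, the model's mean prediction matches the observed rate. With SMOTE it moves most of the way to 50%, the test that the plan names rejects every time for rates from 10% to 40%, and AUC does not improve. Above 50% the non-event class is the minority, so by the same formula the multiplier falls below 1 and risks are understated.

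**The case against.** The best case for the plan is that this is a condensed article. Resampling within training folds followed by recalibration is a defensible approach, and that detail usually sits in the full protocol or analysis plan. The article does not tie SMOTE to the Rankin outcome or state a 1:1 target. The primary classes could also become unequal in first-ever-stroke analyses, because patients with a previous stroke are enrolled but excluded there. A calibration check on real data that exposed the shift would be doing its job.

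Much of this stands, and it limits the size of the point. It does not remove the point. SMOTE is a stated commitment, made without a target outcome and beside two other commitments that it works against. Wherever the imbalance arises, the same shift follows unless it is corrected.

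A reader might infer more than the documents support:

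- **Leakage into cross-validation.** Feature selection, resampling and cross-validation are described in that sequence, which might suggest that synthetic records are made before the folds are split. The sentences describe methods and fix no order of operations, so inflated performance cannot be charged to this plan.
- **Impossible values for binary predictors.** This depends on the SMOTE variant, which is not named; mixed-type variants exist.
- **A broken promise of calibrated risks.** The article says that calibration will be assessed and that risk scores will be provided. It does not promise that the scores will be calibrated.
- **Poor outcome always overstated.** That holds only for event rates below 50%.

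**Conclusion.** The point holds as a conflict between stated methods. In the full primary set SMOTE is idle: zero records are added and no harm is done. For any outcome or subset with a minority class, oversampling towards 1:1 moves predicted risks towards 50% unless they are corrected afterwards. For event rates of 10% to 40%, mean predicted risk would be about 42% to 48%, with no gain in discrimination.

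The existence of the shift follows from the arithmetic of the odds. Its size rests on assumed event rates, an assumed 1:1 target and a logistic model. The article's own learners (neural networks, random forest, gradient boosting) may differ in degree, and a milder target ratio would give a smaller shift. Recalibration to the observed rate would remove it.

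Separately, 1:1 case-control sampling means that predicted probabilities of stroke occurrence are not population risks even without SMOTE. Removing SMOTE does not cure that.

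**What to change.** Remove SMOTE and the other resampling methods from the main models. Suggested wording:

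> Models will be trained on the data as sampled, without resampling. The classification threshold will be chosen from the predicted probabilities, using training data only, to reach a pre-stated sensitivity.

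If resampling is kept, for example as a sensitivity analysis, the plan should:

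1. name the outcome or subset and the target ratio;
2. confine resampling to the training folds;
3. recalibrate predictions to the observed event rate;
4. assess calibration and every performance measure on held-out data that have not been resampled.

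The cost is a few lines of text and somewhat less computing, with no effect on recruitment or data collection. The one small downside is that sensitivity at the default threshold of 0.5 may be lower for an uncommon outcome; the chosen threshold deals with that.
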